	**Time point**							
**Study step**	**Screening and baseline phenotyping**			**Weight loss**	**Weight maintenance**			**Follow-up**
**Visit**	**Screening**	**V1A**	**V1B**	**V2**	**V3A**	**V3B**	**V3C**	**V4**
**Parameters**								
Screening questionnaire	x							
Verify eligibility	x	x	x					
Informed consent	x	x						
Anthropometry		x		x	x	x	x	x
Body height		x						
Bodyweight		x		x	x	x	x	x
Body composition^a^		x		x	x	x	x	x
Body circumferences^b^		x		x	x	x	x	x
Vital parameters		x	x	x			x	x
SBP, DBP		x	x	x			x	x
Heart rate		x	x	x			x	x
Body temperature		(x)^*^	(x)^*^	x			x	x
Respiratory rate		(x)^*^	(x)^*^	x			x	x
Biomaterials		x	x	x	x	x	x	x
Blood		x	x	x	x	x	x	x
Urine			x	x	x		x	
Saliva			x	x			x	
DBS		x		x			x	
24-h urine (optional)			x	x	x		x	
Stool (optional)			x	x			x	
PBMCs (subgroup)		x	x	x			x	
Metabolic response								
Glucose tolerance test		(x)^*^	(x)^*^					
Lipid tolerance test		(x)^*^	(x)^*^					
Questionnaires		x	x	x	x	x	x	x
BAS			x	x	x	x	x	x
DEBQ			x	x	x	x	x	x
EDE-Q8		x						
IWQOL-lite			x	x	x	x	x	x
MBSRQ-AS			x	x	x	x	x	x
mYFAS 2.0			x	x	x	x	x	x
PHQ-9			x				x	
Nutritional assessment		x		x	x	x	x	x
FFQ		x						x
Dietary diary				x				
Dietary record					x	x	x	
PA assessment		x	x	x	x	x	x	x
MoMo		x		x	x	x	x	x
7-day step log			x	x	x	x	x	
RMR		(x)^*^	(x)^*^	x			x	x
Hand strength		(x)^*^	(x)^*^	x			x	
CGM				x				
Functional tests (optional)			x	x			x	
MRI (optional)			x	x			x	
Safety record				x	x	x	x	

*BAS, body appreciation scale; CGM, continuous glucose monitor; DBS, dried blood spots; DBP, diastolic blood pressure; DEBQ, dutch eating behavior questionnaire; EDE-Q8, eating disorder examination questionnaire; FFQ, food frequency questionnaire; IWQOL-lite, impact of weight on quality of life-lite questionnaire; MBSRQ-AS, multidimensional body-self relations questionnaire—appearance scales; MoMo, motoric-module questionnaire; MRI, magnetic resonance imaging; mYFAS 2.0, modified yale food addiction scale version 2.0; PA, physical activity; PBMCs, peripheral blood mononuclear cells; PHQ-9, patient health questionnaire—depression module; RMR, resting metabolic rate; SBP, systolic blood pressure*.

* *Order of measurements dependent on randomization*.

a *Body composition: fat mass, fat-free mass, total body water, impedance*.

b *Waist circumference, hip circumference*.

**Table 3 T3:** Routine blood and urine parameters.

	**Time point**						
**Study step**	**Screening and baseline phenotyping**		**Weight loss**	**Weight maintenance**			**Follow-up**
**Visit**	**V1A**	**V1B**	**V2**	**V3A**	**V3B**	**V3C**	**V4**
**Blood parameters**							
CBC	x		x	x	x	x	x
AST	x		x	x	x	x	x
ALT	x		x	x	x	x	x
γ-GT	x		x	x	x	x	x
AP	x		x	x	x	x	x
Sodium	x		x	x	x	x	x
Potassium	x		x	x	x	x	x
Calcium	x		x	x	x	x	x
Albumin	x		x				
Creatinine	x		x	x	x	x	x
GFR	x		x	x	x	x	x
Urea	x		x	x	x	x	x
Uric acid	x		x	x	x	x	x
Total protein	x		x	x	x	x	x
Bilirubin	x		x				
CRP	x		x	x	x	x	x
HbA1c	x		x	x	x	x	x
TSH	x		x			x	x
T3	x		x			x	x
T4	x		x			x	x
Glucose	x^*^	x^*^	x	x	x	x	x
Total cholesterol	x^*^	x^*^	x	x	x	x	x
Triacylglycerol	x^*^	x^*^	x	x	x	x	x
HDL-C	x^*^	x^*^	x	x	x	x	x
LDL-C	x^*^	x^*^	x	x	x	x	x
LDL/HDL ratio	x^*^	x^*^	x	x	x	x	x
Insulin	x^*^	x^*^	x	x	x	x	x
**Urine parameters**							
Albumin		x	x				
Creatinine		x	x	x		x	
Urea		x	x	x		x	
Urea nitrogen		x	x	x		x	

*ALT, alanine aminotransferase; AP, alkaline phosphatase; AST, aspartate aminotransferase; CBC, complete blood count; CRP, C-reactive protein; γ-GT, gamma-glutamyltransferase; GFR, glomerular filtration rate; GOT, glutamic oxalacetic transaminase; GPT, glutamic pyruvate transaminase; HbA1c, hemoglobin A1c; HDL-C, high-density lipoprotein cholesterol; LDL-C, low-density lipoprotein cholesterol; TSH, thyroid-stimulating hormone; T4, thyroxine; T3, triiodothyronine*.

* *Several time points are available for these parameters, since they will be analyzed as part of the meal challenge*.

Further exploratory research questions are planned and will be clarified in the course of the study.

### Sample Size and Power Calculation

A total of 252 participants will be randomized to the weight maintenance step (*n* = 63 per arm). Assuming a 30% dropout, there will be 176 participants (*n* = 44 per arm) that provide primary endpoint data. A sample size of 176 participants is sufficient to detect a difference in weight loss maintenance of 1.7 kg between the two dietary intervention arms and the two digital tools with a power of 80%, a significance level of 0.05 and assuming a within-arm standard deviation of 4.0 kg.

To randomize 252 participants to the weight loss maintenance step, it is estimated that 504 participants are needed to be included in the weight loss step. This estimate is based upon the assumption that 30% of participants will drop out during weight loss and that 20% will not reach the weight loss of 4 kg, which is necessary for randomization to one of the four weight maintenance groups. These are conservative estimates for dropout and ineligibility. If these rates are lower, fewer people will need to be screened and included in the weight loss step.

### Randomization

There are two randomization time points (Figure 2). The first randomization takes place at baseline, shortly before the participant attends the first visit and determines either the order of the two meal challenges (OGTT and lipid meal challenge) as well as the type of the lipid meal challenge (plain lipid drink or a glucose-lipid mixed drink). The second randomization takes place after weight loss during visit V2, in which participants are randomly assigned to one of the four weight maintenance intervention arms. This randomization step is stratified according to the order and type of meal challenges assigned with the first randomization. The results of the meal challenge tests (e.g., glucose response) are not considered for the weight maintenance intervention.

For each randomization, an online tool of the Münchner Studienzentrum (MSZ) is used to generate the allocation sequences. This online tool uses pre-defined randomization lists, created block-wise. Due to the nature of the intervention, it is not possible to blind the participants as well as the study team.

### Data Collection

Measurements and data collection occur during seven face-to-face visits throughout the study. These visits are numbered according to the study step (I–IV). If there are more than one visit assigned to a study step, they are additionally labeled in alphabetical order (A-C). Participants attend the visits fasted for at least 8 h, without being physically active in the past 12 h and no smoking on the day of the visit. Table 2 gives an overview of data collected at different time points in the study.

#### Anthropometry

Height (cm) is measured in a standing position, without shoes and looking straight using a stadiometer (Seca 214, Seca GmbH & Co., KG, Germany).

Body composition is assessed in a fasted state using a body composition scale (BC-418MA, Tanita Europe B.V., Netherlands), based on the Bioimpedance analysis (BIA). The participant is asked to take off shoes and empty the bladder before measurement. Since the participant is allowed to be dressed in light clothing, one kilogram is deducted for the assessment. The following data outcomes are recorded: weight (kg), fat mass (%, kg), fat-free mass (kg), total body water (kg), and impedance (Ω).

Waist and hip circumferences (cm) are measured in a standing position using a non-stretch measuring tape with a hock for easier reading.

Furthermore, participants are invited to an optional MRI measurement to determine e.g., fat distribution, organ fat (e.g., liver fat content), and brown adipose tissue (e.g., proton density fat fraction).

Additionally, optional phenotyping concerning muscular strength, motor function and posture analysis are assessed through different techniques: Body Composition using an air displacement plethysmograph (BOD POD, Cosmed S.r.l., Italy) and a body composition analyzer (InBody 770, InBody Europe B.V., Germany), posture analysis using a 3D Body Scanner (VITUS 3D Body scanner, Vitronic, Germany) and the Diers scan (DIERS formetric 4D, DIERS International GmbH, Germany) and motor and muscle function using a 3D force plate (OPTIMA force plate, Advanced Mechanical Technology Inc., AMTI, USA), and the IsoMed Back Module (D. & R. Ferstl GmbH, Germany).

#### Vital Parameters

Systolic and diastolic blood pressure (mmHg) and heart rate (bpm) are carried out in a seating position using a blood pressure monitor (BM 60 or BM 70, BEURER GmbH, Germany; M400 Intelli IT, OMRON Medizintechnik Handelsgesellschaft mbH, Germany) with a cuff. Blood pressure is calculated as the mean value of 3 performed measurements on the arm with the higher blood pressure measured with a 1-min rest in between. Body temperature (°C) is measured with an in-ear infrared thermometer (Thermoscan IRT 4020, Braun GmbH, Germany). The respiratory rate measurement is carried out manually by counting the patient's breath rate per minute.

#### Biomaterials

Fasting venous blood, fasting midstream urine and 24 h urine samples are collected and sent to an external lab (SYNLAB Medizinisches Versorgungszentrum Labor München Zentrum GbR, Munich, Germany) for the analysis of routine parameters (Table 2). Furthermore, serum and plasma blood samples, peripheral blood mononuclear cells (PBMCs), dried blood spots (DBS) and urine samples are stored at −80°C until needed for further analysis. PBMCs however, will be gradually frozen at −80°C in a separate freezing container (Nalgene® [name]® Cryo 1°C Freezing Container, Thermo Fisher Scientific Inc., USA) for the first 3 days and transferred to a liquid nitrogen tank after the third day. Sample collection, pre-analytic steps, labeling, storage, packing, and shipment of samples is performed according to standard operating procedures (SOPs).

Additionally, saliva samples are collected in a fasting state (Table 3). Participants spit about 1–2 ml directly into a tube with a screw cap. Saliva samples are stored at −80°C until analysis.

Participants are also invited to collect stool samples at home. Samples are collected in tubes with and without a DNA stabilizer. Samples will be stored at −80°C until analysis.

#### Questionnaires

German versions of the following questionnaires are applied once or several times throughout the study course: Body Appreciation Scale (BAS) (23), the Dutch Eating Behavior Questionnaire (DEBQ) (24), the short version of the Eating Disorder Examination Questionnaire (EDE-Q8) (25), impact of weight on quality of life-lite questionnaire (IWQOL-lite) (26), the Multidimensional Body-Self Relations Questionnaire—Appearance Scales (MBSRQ-AS) (27), Modified Yale Food Addiction Scale Version 2.0 (mYFAS 2.0) (28, 29), the Patient Health Questionnaire—Depression module (PHQ-9) (30, 31), and the Motorik-Modul (MoMo) questionnaire (32, 33). Additionally, questionnaires to assess medical history, social-economic factors (e.g., marital status, qualification, employment, smoking status), safety and an evaluation of the study program are filled out by participants.

#### Lifestyle Assessment

Dietary intake is assessed in each step of the LION Study using different methods. A food frequency questionnaire (FFQ) is used (Visits V1A and V4) to obtain an overview of the participant's diet history (34). A daily dietary record is filled in during the weight-loss intervention to assess the intake of formula diet products, vegetables, and beverages and to collect data on well-being. Furthermore, open dietary records for 3 consecutive days are applied three times during weight maintenance, to assess total energy intake and the participants' adherence to their assigned weight maintenance diet.

Moreover, participants are encouraged to use any tool of choice (e.g., wearables, apps) to track physical activity and document daily steps in a 7-day step log at five time points.

#### Resting Metabolic Rate (RMR)

The RMR is measured through indirect calorimetry (COSMED Quark RMR 2013010303, COSMED S.r.l., Italy) with a canopy hood. Based on the measured oxygen consumption (VO_2_) and carbon dioxide production (VCO_2_) and using the equation after Weir (35), the software calculates RMR (kcal/day). The 30-min measurement is carried out after an overnight fast in a lying position at rest.

#### Handgrip Strength

Handgrip strength (kg) is measured with a handgrip dynamometer based on a hydraulic system (JAMAR®, Performance Health Supply Inc., USA). The measurement takes place in a seated position with the elbow flexed at 90° and rested on an armrest. The participant is instructed to press as hard as possible for a short period. The measurement is repeated six times (three times each arm). The maximum isometric strength of the hand and forearm muscles is the highest value of the six measurements.

#### Continuous Glucose Monitoring (CGM)

For CGM participants wear a small sensor (FreeStyle Libre Pro, Abbott Diabetes Care Inc., USA) on the back of the upper arm, during the first 4 weeks of formula diet. The sensor consists of a thin, flexible filament (0.4 × 5 mm) which is inserted, activated, and replaced by the study team in the uppermost skin layer and automatically monitors blood glucose levels (mg/dl) in the interstitial fluid continuously. Collected data are used for exploratory analyses and has no impact on the weight loss or weight maintenance intervention. Diabetes status, as an important factor associated with overweight and obesity, will be monitored through routine blood parameters collected during face-to-face visits.

### Data Management

Data management, monitoring, and randomization are conducted in cooperation with the local coordinating center for clinical studies, the Münchner Studienzentrum (MSZ), which is a member of the nationwide network of clinical coordinating centers (KKS). Most data are completed on hard copy case report forms (CRFs) and are subsequently entered into an electronic database (MACRO 4, InferMed Ltd., UK) by the study team. Access rights and login criteria are defined. Monitoring is carried out by the MSZ according to a monitoring plan.

### Statistical Analysis

To investigate the primary outcome, a comparison of groups in the weight maintenance step (app groups combined vs. newsletter groups combined and low carb groups combined vs. low fat groups combined at month 15) will be conducted based upon a linear regression model. A further regression model assesses a potential interaction between the dietary and mode of delivery interventions. A complete-case analysis and analysis using multiple imputations will be performed. Participants are analyzed according to groups to which they are randomized (intent-to-treat, ITT).

The continuous secondary endpoints at different time points are compared between the dietary and the mode of delivery groups using analogous linear regression models in complete-case analyses.

Exploratory analyses are performed to assess parameters as potential predictors for effective weight loss and weight maintenance. Exploratory analysis can be restricted to subgroups based on a per-protocol analysis. For instance, to address the bias of self-reported data obtained due to the implementation of telephone-based visits during the coronavirus pandemic, the mode of visits will be considered in statistical analysis (e.g., by adjusting according to the mode of the visit). Moreover, interaction terms (e.g., gene-diet interactions) will be considered as exploratory analyses. Since further weight loss is allowed during weight maintenance, weight trajectories during this period will be also one element of subgroup analysis (e.g., weight loss, stable weight, weight regain).

Finally, missing data are a challenge in long-term clinical studies. Depending on the amount of acquired missing data, statistical analysis will be adapted (e.g., imputation).

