The daily energy requirement is calculated for each participant individually, based on the measured resting metabolic rate (RMR) after weight loss multiplied with the individual's physical activity level (PAL). The PAL is chosen based on the PAL values for work and leisure activities of the German Nutrition Society, according to self-reported work, leisure, and physical activities. However, the recommended daily energy intake in the weight maintenance period is 10% lower than the calculated daily energy requirement (recommended daily energy intake = (RMR x PAL) – 10%). The reduction by 10% serves as a safety buffer to ensure weight maintenance, to diminish known inaccuracies in the calculation of energy requirements. If desired, further weight loss is allowed during the weight maintenance step, provided that it is performed within the framework of the weight maintenance intervention. The participant's compliance is estimated based on the recurring determination of blood and urine parameters (e.g., urea concentration for protein intake), and macronutrient composition of total energy intake assessed by a dietary record at three time points during the 12-month weight maintenance step. At months 6, 9, and 15 participants are examined in face-to-face visits (Visit 3A, 3B, and 3C).

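### Continuous secondary endpoints get visit-by-visit complete-case regressions despite 30% planned dropout, and the clause allowing imputation has no trigger or endpoint scope

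*Protocol article*

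**What the plan says.** All of the relevant analysis text is in the article's Statistical Analysis section.

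- Primary endpoint (month 15): "A complete-case analysis and analysis using multiple imputations will be performed".
- Secondary endpoints: the continuous ones, at the various time points, "are compared between the dietary and the mode of delivery groups using analogous linear regression models in complete-case analyses". No imputation or repeated-measures model is named for them.
- Population: "Participants are analyzed according to groups to which they are randomized (intent-to-treat, ITT".
- Last sentence of the section: "Depending on the amount of acquired missing data, statistical analysis will be adapted (e.g., imputation". It does not say what amount of missing data triggers a change, or which endpoints it covers.

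On attrition, Sample Size and Power Calculation states: "Assuming a 30% dropout, there will be 176 participants". On visits, Weight Maintenance Intervention states: "At months 6, 9, and 15 participants are examined in face-to-face visits (Visit 3A, 3B, and 3C"; Visit 4 follows at month 27. Table 2 schedules weight, body composition and circumferences at V2, V3A, V3B, V3C and V4, and Table 3 does the same for most blood values.

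**The concern.** The plan treats missing data more carefully for the primary endpoint than for the continuous secondary endpoints, although the same people leave. A regression at month 15 or month 27 restricted to those seen at that visit ignores what a dropout recorded at months 6 and 9. Those values could be informative, because regain seen at month 9 may predict both leaving and later weight. The analysed set can also change from visit to visit, so group differences at months 6, 9, 15 and 27 need not refer to the same participants. Assignment is respected as the intent-to-treat sentence requires, but randomized people without a value at that visit are left out.

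Dropout could plausibly relate to weight differently by group. The app groups have a personal coach and a chat, whereas the newsletter groups receive emails. If so, the between-group contrast itself is at risk. The exposure is probably greatest at month 27, the visit furthest from randomization, and the Discussion counts this long follow-up among the strengths.

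**Working it through.** **The plan's own figures.** Inputs from Sample Size and Power Calculation: difference 1.7 kg, SD 4.0 kg, power 80%, significance level 0.05 (two-sided assumed), dropout 30%.

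- Per pooled group: n = 2 × (1.960 + 0.842)² × 4.0² / 1.7² = 2 × 7.85 × 16 / 2.89 = 86.9, so 87 and 174 in total. The article states 176. With 88 against 88 the power is 0.805 (normal approximation) or 0.801 (t-test).
- Randomized: 176 / 0.70 = 251.4, so 252, as stated.
- Absent from a month-15 complete-case analysis at the planned rate: 252 − 176 = 76, and 76 / 252 = 30%.

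These figures reproduce. The point concerns the method, and none of them changes.

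**Illustration of the possible bias.** The documents do not give visit-specific SDs, between-visit correlations or a dropout mechanism, so the following are assumptions:

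- 2,000 simulated trials per scenario, 126 against 126, three visits.
- SDs 2.5, 3.2 and 4.0 kg. Only 4.0 comes from the article.
- Correlation 0.7 between adjacent visits and 0.7² = 0.49 between the first and third.
- Random 10% loss at the first visit. After that, the log-odds of leaving are −1.95 + slope × (previous value / its SD), where a positive slope means that heavier participants leave more often.
- With slope 0 the loss per step is 1 / (1 + e^1.95) = 12.5%, so total loss is 1 − 0.90 × 0.875² = 31%, close to the planned 30%.

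The two values in a cell are for a true difference of 0 and of −1.7 kg. Bias is in the third-visit group difference.

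| Slope, group A / B | Loss A / B (%) | Complete-case bias (kg) | Bias using earlier visits (kg) |
|---|---|---|---|
| 0 / 0 | 31/31; 31/31 | −0.02; −0.03 | −0.02; −0.03 |
| 0.7 / 0.7 | 34/34; 34/30 | 0.01; 0.09 | 0.01; 0.02 |
| 1 / 0.5 | 36/32; 35/30 | 0.34; 0.34 | 0.01; −0.01 |
| 0.7 / 0 | 34/31; 34/31 | 0.44; 0.43 | 0.00; −0.01 |
| 1 / 0 | 36/31; 36/31 | 0.62; 0.63 | −0.01; 0.00 |

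- The Monte Carlo error of each bias is about 0.6 / √2000 = 0.013 kg.
- Where dropout depended on earlier weight alike in both groups, each arm mean was too low by 0.35 to 0.44 kg, but this nearly cancelled in the contrast.
- Where the dependence differed, the contrast was off by 0.34 to 0.63 kg. Against 1.7 kg that is 0.34 / 1.7 = 20% to 0.63 / 1.7 = 37%. In SD units it is 0.34 / 4.0 = 0.09 to 0.63 / 4.0 = 0.16.
- The likelihood estimate using earlier visits had a standard error between equal and about 4% smaller. Its bias is near zero partly by construction, because dropout in the simulation depends only on observed values.

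**The case against.** The strongest reply is that the text is narrower and more flexible than it first looks. Four stronger readings are tempting, and the documents do not support them.

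- *Every secondary endpoint is complete-case.* The sentence covers continuous endpoints compared between groups. The predictor analyses, which make up most of the secondary objectives, are described separately as exploratory, with no such rule.
- *Complete-case is the only method allowed.* The closing sentence permits adaptation, including imputation. Since the primary already has multiple imputation, its natural use is elsewhere. This stands as a correction, but the sentence has no trigger or scope, and it postpones the choice in a trial whose study team is unblinded. It does not replace the rule that is stated.
- *Intermediate data are thrown away.* Month-6 and month-9 values are analysed at their own visits. They are only not used for later ones.
- *The results will be biased by a kilogram or more.* Multiplying 30% dropout by a supposed gap between leavers and stayers gives an error in an arm mean. The documents give no such gap and no month-27 loss rate. The planned estimate is a between-group contrast, in which equal dropout with an equal gap cancels.

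It is also true that a correctly specified complete-case regression is unbiased when missingness depends only on covariates in the model, such as the V2 value. Phone visits with self-reported data may reduce missing weights. Hand strength, PHQ-9 and MRI have one post-randomization visit (V3C), so a repeated-measures model adds essentially nothing for them. Complete-case analysis of unpowered secondary endpoints is common. These points limit the size and reach of the concern. They do not explain why a weaker method is named for endpoints whose earlier values are already collected.

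**Conclusion.** The point holds in limited form. For continuous secondary endpoints measured repeatedly after randomization, the plan names a method that does not use available earlier data for later visits, in a trial that expects to lose 30% by month 15. Its only escape clause is undefined. A full analysis plan, not shown, may add detail, but the article does state the method, so this is a choice that can be judged rather than an omission.

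The bias in the contrast could be negligible or could reach about 0.6 kg on the assumed scenarios. The upper end requires dropout to depend on earlier weight differently by group, which the documents make plausible but do not show. The kilogram figures use the month-15 SD. The documents give no SD for month 27 or for non-weight endpoints, so they do not carry over directly. The precision gain from the better method is small; the reason to change is robustness. The change should be made, but the powered month-15 comparison, which already has multiple imputation, is not affected.

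**What to change.** - **Endpoints with two or more post-randomization visits** (for example weight, body composition, circumferences, most blood values): replace the complete-case wording with one mixed model for repeated measures per endpoint. Use the visits at which it is measured, diet-by-visit and tool-by-visit terms and the V2 value as covariate, and include all randomized participants with at least one post-randomization value. Alternatively, apply the primary's multiple imputation with earlier visits in the imputation model. Keep the complete-case regressions as a sensitivity analysis.
- **Endpoints with a single post-randomization visit** (hand strength, PHQ-9, MRI): use multiple imputation or keep complete-case, and say which.
- **Closing sentence**: limit it to named endpoints and a stated condition, fixed before outcome data are compared by group, or delete it once the two rules above are in place.

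The cost is plan wording and modest programming, with no new data. Both replacements assume that data are missing at random given what was observed. They do not cure dropout driven by regain that occurs after the last recorded visit, which matters most over the 12 months between V3C and V4.
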